#### 1.1.3. Vowel Processing

Vowels are primarily distinguished by their first and second formants (F1 and F2). Research shows that children with ASD demonstrate significant differences in vowel processing across multiple levels, ranging from early sensory encoding to higher-order attentional mechanisms [34]. There is evidence that intact MMN responses to vowel contrasts can be found in some individuals with ASD, especially in high-functioning cohorts without language impairment. However, differences in MMN latency, amplitude, or hemispheric lateralization are also reported, particularly in ASD subgroups with more pronounced language difficulties [3,35]. These inconsistencies may stem from variations in the population studied (e.g., language ability), stimulus design, and analysis methods.

Compared to their TD peers, children with ASD show prolonged MMN latencies in response to vowel deviants, indicating delayed neural encoding of relatively steady formant structure [36,37]. Attentional mechanisms are also affected. The P3a component, which follows MMN and reflects automatic attention shift [38,39], is reduced in response to vowel (but not non-speech) deviants in ASD [32,40,41]. This pattern points to a speech-specific problem in attentional engagement, suggesting that while basic acoustic change detection may be preserved, the subsequent allocation of attention to speech-relevant changes is diminished.

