#### 2.1.2. Inclusion and Exclusion Criteria

ASD Group: A total of 30 children diagnosed with ASD according to DSM-5 criteria (28 males, 2 females; age range: 9–14) will be recruited from Guangzhou Kangna School. Participants met the DSM-5 diagnostic criteria for ASD [1]. The Chinese version of the Gilliam Autism Rating Scale, Second Edition (GARS-2) [68] will be used, which includes three subscales: Stereotyped Behaviors, Communication, and Social Interaction. Scoring is based on DSM-IV-TR [69] and standards from the Autism Society of America (1994). The GARS-2 has shown good validity within the Chinese ASD population [70]. Non-verbal intelligence was assessed using the standard version of the Raven Progressive Matrices, and the scores were within the normal range (percentile ≥ 25).

TD Group: A total of 30 children with no history of neurological or psychiatric disorders (28 males, 2 females; age range: 9–14) will be recruited from Guangzhou Yongxing Primary School. The TD group and ASD group are matched for gender ratio (male: female = 28:2), age (no significant difference between groups as determined by independent samples t-test), and non-verbal intelligence (Raven test scores matched). All participants are native speakers of Mandarin Chinese and right-handed.

Participants will be excluded if they have any of the following conditions: uncorrected hearing impairment, a history of epilepsy or other neurological disorders, hearing abnormalities as indicated by a pure-tone audiometry threshold greater than 25 dB HL, or an inability to cooperate with the experimental tasks, such as excessive head movement or a gaze rate below 70%.

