The pattern of results will be evaluated against two complementary sets of predictions. If the theory-driven framework (EPF/WCC/NCH) is supported, we expect to see a dissociation: relatively intact or enhanced neural responses (e.g., MMN amplitude, factor scores) to single-feature deviants (e.g., consonant-only, vowel-only), but attenuated or delayed responses to multi-feature deviants (e.g., V + T, C + V + T). This pattern would align with models that posit a cognitive style in ASD characterized by heightened local sensitivity paired with impaired global integration. It would suggest that children with ASD can detect individual phonetic cues but struggle to bind them into unified, linguistically meaningful percepts. If the data-driven framework (MMN literature) is supported, we expect to see a graded, complexity-dependent deficit: reduced MMN amplitudes and prolonged latencies across all conditions, with the most severe effects in multi-feature and tone-involving contrasts. This would be consistent with the Neural Complexity Hypothesis and would suggest a more general processing burden in ASD, where increasing feature complexity leads to cumulative degradation in neural responsiveness, regardless of a local/global distinction. If the results reveal a mixed or unexpected pattern (e.g., no group difference in tone processing), this would highlight the heterogeneity within the ASD population and challenge the universality of current models. Such findings would prompt a re-evaluation of assumptions about what constitutes “local” or “global” processing and could point to subgroup-specific profiles (e.g., based on language ability or sensory preference) that are not captured by broad theoretical frameworks.

A key aspect of our analysis is the inclusion of hemispheric asymmetry as a data-driven prediction. While EPF, WCC, and NCH do not explicitly predict reduced left-hemispheric specialization, the MMN literature suggests that children with ASD may show less lateralized or right-shifted MMN responses to speech sounds. If this is confirmed, it would provide critical evidence for atypical neural organization in ASD, one that may underlie broader difficulties in processing rapid, temporally precise linguistic cues.

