While the multi-feature oddball paradigm is well-validated in developmental and clinical populations, we acknowledge that detecting fine-grained differences in MMN is challenging. Our analytical approach is designed to maximize sensitivity, but the results must be interpreted within the context of known variability in ASD and the inherent limitations of EEG. Foundational studies [62,81] demonstrated that multi-feature paradigms efficiently detect various speech-sound differences with comparable or superior sensitivity to traditional paradigms, using shorter recording times. More recent work [1,2] has refined these paradigms to capture fine-grained phonetic and prosodic contrasts, sensitive to individual variability in language and musical experience. Critically, studies applying this approach in children at risk for dyslexia [63], children with Asperger syndrome [82], and very young children or infants [83,84], confirm the method’s reliability across ages and populations. Cross-linguistic applications [85] and recent work on emotional prosody [65,86] further demonstrate its feasibility in capturing subtle speech-feature processing differences across linguistic and developmental contexts. Building on this empirical foundation, we employ advanced analytic approaches (t-PCA, RSA) to further enhance sensitivity by isolating latent neural components and distributed representational patterns, thereby increasing the likelihood of detecting group-level differences even when univariate effects are small.

Our carefully matched ASD and TD sample allows us to examine how factors like language ability, symptom severity, and developmental stage modulate neural processing. Testing these predictions in Mandarin, a tonal language where pitch is lexically meaningful, enables a critical test of whether atypical auditory processing in ASD stems from integration deficits (WCC) or enhanced feature detection (EPF)—a distinction with direct implications for intervention. While both EPF and WCC predict reduced responses to multi-feature deviants, they diverge on single-feature processing: EPF predicts enhanced or intact responses, while WCC does not. However, we acknowledge that the existing MMN data suggest that the notions of local vs. global and segmental vs. suprasegmental processing may be oversimplistic. The outcomes may reflect additive or interactive influences among different phonological features.

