Finally, the relatively small sample size and multilevel analytical approach limit our ability to model individual differences comprehensively. Although we aim to collect data on ASD symptom severity (GARS-2), age, and gender, these variables could not be fully included as covariates in formal models due to power constraints. They can be considered in exploratory analyses. Notably, the sample is gender-imbalanced (28 males, 2 females), reflecting the higher male prevalence in ASD but potentially limiting generalizability, especially given known sex differences in auditory processing and ASD phenotypes. A central challenge in studying auditory and speech processing in ASD is the substantial heterogeneity within the population. Children with ASD exhibit a wide range of language outcomes, from minimally verbal to age-appropriate or even advanced language skills. Similarly, auditory hypersensitivity (e.g., distress to loud sounds) is a common sensory feature in ASD, but not universal. Some individuals may show a preference for nonspeech sounds over speech and others may not. This variability is not merely noise to be controlled for; it may be central to understanding the diverse profiles of speech perception. Future studies with larger, demographically balanced samples and integrated behavioral assessments will be essential to validate group/subgroup differences as well as individual differences and extend these findings.

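### A null group contrast is to be read as showing ASD heterogeneity, and modulation by language ability is claimed although no language measure is described

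*Protocol article*

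**What the plan says.** Section 5 presents itself as setting out the frameworks by which the findings will be judged once the data are in. It gives three branches: the theory-driven predictions are supported, the data-driven predictions are supported, or neither fits cleanly. On the third branch it says: "If the results reveal a mixed or unexpected pattern (e.g., no group difference in tone processing), this would highlight the heterogeneity within the ASD population". The same sentence goes on to say that this would call into question whether current models hold universally. The next adds that such findings "could point to subgroup-specific profiles (e.g., based on language ability or sensory preference".

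Later in Section 5 the plan says of its sample: "Our carefully matched ASD and TD sample allows us to examine how factors like language ability, symptom severity, and developmental stage modulate neural processing".

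Section 6 (Limitations and Future Directions) covers the individual-difference data. It names three variables to be recorded, namely severity by GARS-2, the child's age and the child's gender, and then concedes that "these variables could not be fully included as covariates in formal models due to power constraints". It allows these variables in exploratory analyses and leaves combined behavioural assessment to future studies. Section 2.1.2 describes the GARS-2, the Raven matrices, pure-tone audiometry, age and sex. Of the Raven results in the ASD group it says that "the scores were within the normal range (percentile ≥ 25" or above. It also excludes children who cannot cooperate with the task.

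**The concern.** Two inferences are offered that the design does not support.

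First, a missing group difference is given a substantive meaning. A difference in means that fails to reach significance can arise because there is no true difference, because a true difference was missed, or because children vary a great deal. The contrast alone cannot separate these. The third branch names heterogeneity and failure of the models, and has no place for an inconclusive result.

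Second, modulation by language ability is presented as something the sample can show. Matching on sex, age and Raven score supports the comparison of the two groups, but says nothing about how the response varies with language. For that, language must be measured in each child.

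At stake is the wording of the conclusions. A non-significant tone contrast, which is a likely result even if a moderate difference exists, could be reported as a finding about ASD. A statement about language could also be made with no language variable behind it.

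**Working it through.** **The plan's own figure.** Section 2.1.1 gives 52 children in total for f = 0.25, power 0.80 and α = 0.05 in a repeated-measures interaction. The number of measures and their correlation are not stated, so the figure cannot be reproduced. With seven measures, and depending on the convention for f and on the correlation, the required total ranges from 8 to 226. Nothing below depends on it. The checks use the planned 30 per group and one two-group contrast, such as ASD against TD on the tone deviant.

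**Precision of one contrast.** Inputs: 30 and 30 children (Section 2.1.2), 58 degrees of freedom, two-sided 95%.

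- Half-width in SD units = t(0.975, 58) × √(2/30) = 2.002 × 0.2582 = 0.517.
- An observed difference of exactly zero therefore has an interval of about −0.52 to +0.52 SD.
- A contrast that just misses significance has an interval from about 0 to 0.517 + 0.517 = 1.03 SD. Any non-significant contrast thus leaves differences of at least 0.52 SD open in one direction.

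**Chance of missing a real difference.** Two-sample t-test, two-sided α = 0.05, noncentrality d × √(30/2) = 3.873 d.

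| True d | Noncentrality | Power | Missed |
|---|---|---|---|
| 0.3 | 1.16 | 0.21 | 79% |
| 0.5 | 1.94 | 0.48 | 52% |
| 0.74 | 2.87 | 0.80 | 20% |

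The value d = 0.5 is not arbitrary. For two equal groups and a single measure, d = 2f = 2 × 0.25 = 0.5. This is only a reference point, because the plan's f belongs to an interaction. At 26 per group, the plan's minimum, power at d = 0.5 is 0.42.

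**What is claimed against what is described.**

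| Factor in Section 5 | Measure described | Status in Section 6 |
|---|---|---|
| Language ability | None | Not listed |
| Sensory preference | None | Not listed as collected |
| Symptom severity | GARS-2 | Listed, exploratory |
| Developmental stage | Age | Listed, exploratory |

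The GARS-2 has a Communication subscale, but it is a symptom rating described for the ASD group and not a language test.

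**What the exploratory analyses can show.** For a correlation within 30 ASD children, using Fisher's z, the smallest r detectable with 80% power is tanh[(1.960 + 0.842)/√27] = tanh(0.539) = 0.49. Power at r = 0.3 is about 36%. An observed r of zero has an interval of ± tanh(1.960/√27) = ±0.36.

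**The case against.** The plan has real answers. These are Discussion paragraphs, and neither sentence alters a test or a dataset. The subgroup clause is hedged. Section 6 calls the findings preliminary, declines to treat them as decisive for any theory, and admits limited power. A reader might infer that a null would be presented as firm proof; the documents do not support that. The sentence on heterogeneity is nevertheless unhedged, and it belongs to the framework the plan says it will use.

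Heterogeneity may also mean differences between ASD samples. Section 1.1.1 reports reduced tone responses in earlier groups, so a group without the reduction could suggest that it is not universal. That reading is legitimate, but it needs a null precise enough to rule out the reduction, and ±0.52 SD seldom will be.

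Four stronger readings are tempting and should not be made:

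- **That the sample is narrow in language or severity, so that intact responses reflect selection.** Section 2.1.2 restricts neither. Raven is a non-verbal test, and the statement in Section 1.1.3 that "intact MMN responses to vowel contrasts can be found in some individuals with ASD, especially in high-functioning cohorts without language impairment" concerns vowels and children without language impairment.
- **That none of the named modulators can be examined.** Severity and age are recorded.
- **That language is certainly not measured.** The list in Section 6 is not declared complete, and Section 2.1.1 mentions behavioural data. The defect is that the claim has no described measure behind it.
- **That the plan must add a test of between-child variance or a correlation with GARS-2 Communication.** Group differences in EEG noise would confound the first even at equal epoch counts. The second would be underpowered and is a matter of preference.

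The power figures describe a single contrast and not the planned repeated-measures analysis. That limits their scope, but the plan's own example is a single contrast of this kind.

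**Conclusion.** The concern holds for two statements in Section 5. The reading given to a null or mixed pattern does not follow from a comparison of means: with 30 per group the interval is about ±0.52 SD, and a true difference of 0.5 SD is missed about 52% of the time. The claim about language ability conflicts with Sections 2.1.2 and 6, which describe no such measure.

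The figures assume 30 analysable children in each group, a two-sided 5% test, one approximately normal measure and no multiplicity correction. Losses or a correction would lower the power. The group comparison itself is unaffected. What changes is what the study may conclude from a likely result.

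**What to change.** 1. Replace the third branch in Section 5. Report a non-significant contrast with its 95% confidence interval and call it inconclusive unless the interval excludes a margin stated in advance. Do not infer heterogeneity or subgroup profiles from a null group contrast. When choosing the margin, note that with 30 per group no margin below about 0.52 SD can be excluded in both directions.
2. Remove language ability from the claim about the sample, unless a language measure is in fact collected, in which case name it. Describe severity and age as exploratory only, in line with Section 6.
3. Limit conclusions to children with ASD at Raven percentile ≥ 25 who can complete the session.

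The cost is a few sentences and the choice of one margin, with no new recruitment, testing or analysis. The downside is that a null result supports a weaker statement, and many nulls will have to be called inconclusive.

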## 6. Limitations and Future Directions

Several limitations should be acknowledged. First, as with many ERP studies involving clinical populations, sample sizes, particularly within the ASD group, may limit statistical power, especially for detecting nuanced interaction effects. Mitigation strategies include the use of permutation-based statistical corrections and robust within-subject analyses. Second, ERP morphological variability across participants may complicate t-PCA component matching, potentially affecting component stability and RDM construction consistency. Efforts are made to standardize preprocessing and component validation procedures. Third, theoretical RDMs employed in RSA may oversimplify the complex acoustic–phonetic realities of natural speech, potentially affecting ecological validity. Future work could refine these models to encompass finer-grained acoustic and linguistic parameters.

Furthermore, the complex interactions among phonological features (tone, vowel, consonant) may exceed the explanatory scope of current cognitive frameworks such as EPF and WCC. Our study is exploratory in nature, designed not to definitively test these broad theories in their entirety, but to derive and evaluate specific, constrained predictions about local versus global auditory encoding. Findings should therefore be interpreted as preliminary insights into neural processing differences, rather than conclusive evidence for or against any single theoretical account.

Additionally, while the multi-feature oddball paradigm enables precise manipulation of phonological features, it uses isolated syllables in a passive listening context, which lacks the temporal, syntactic, and semantic richness of natural communication. We acknowledge that this design does not fully capture real-world language processing and is not equipped to test high-level cognitive models (e.g., Bayesian Predictive Coding [87,88,89]) in their complete form. Instead, it provides a controlled, developmentally sensitive window into early auditory integration. Future research should extend these findings using connected speech, predictive paradigms, or naturalistic listening tasks [90,91].

Finally, the relatively small sample size and multilevel analytical approach limit our ability to model individual differences comprehensively. Although we aim to collect data on ASD symptom severity (GARS-2), age, and gender, these variables could not be fully included as covariates in formal models due to power constraints. They can be considered in exploratory analyses. Notably, the sample is gender-imbalanced (28 males, 2 females), reflecting the higher male prevalence in ASD but potentially limiting generalizability, especially given known sex differences in auditory processing and ASD phenotypes. A central challenge in studying auditory and speech processing in ASD is the substantial heterogeneity within the population. Children with ASD exhibit a wide range of language outcomes, from minimally verbal to age-appropriate or even advanced language skills. Similarly, auditory hypersensitivity (e.g., distress to loud sounds) is a common sensory feature in ASD, but not universal. Some individuals may show a preference for nonspeech sounds over speech and others may not. This variability is not merely noise to be controlled for; it may be central to understanding the diverse profiles of speech perception. Future studies with larger, demographically balanced samples and integrated behavioral assessments will be essential to validate group/subgroup differences as well as individual differences and extend these findings.

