## Abstract

**Background/Objectives:** Children with Autism Spectrum Disorder (ASD) often display heightened sensitivity to simple auditory stimuli, but have difficulty discriminating and integrating multiple phonological features (segmental: consonants and vowels; suprasegmental: lexical tones) at the syllable level, which negatively impacts their communication. This study aims to investigate the neural basis of segmental, suprasegmental and combinatorial speech processing challenges in Mandarin-speaking children with ASD compared with typically developing (TD) peers. **Methods:** Thirty children with ASD and thirty TD peers will complete a multi-feature oddball paradigm to elicit auditory ERP during passive listening. Stimuli include syllables with single (e.g., vowel only), dual (e.g., vowel + tone), and triple (consonant + vowel + tone) phonological deviations. Neural responses will be analyzed using temporal principal component analysis (t-PCA) to isolate overlapping ERP components (early/late MMN), and representational similarity analysis (RSA) to assess group differences in neural representational structure across feature conditions. **Expected Outcomes:** We adopt a dual-framework approach to hypothesis generation. First, from a theory-driven perspective, we integrate three complementary models, Enhanced Perceptual Functioning (EPF), Weak Central Coherence (WCC), and the Neural Complexity Hypothesis (NCH), to account for auditory processing in ASD. Specifically, we hypothesize that ASD children will show enhanced or intact neural discriminatory responses to isolated segmental deviations (e.g., vowel), but attenuated or delayed responses to suprasegmental (e.g., tone) and multi-feature deviants, with the most severe disruptions occurring in complex, multi-feature conditions. Second, from an empirically grounded, data-driven perspective, we derive our central hypothesis directly from the mismatch negativity (MMN) literature, which suggests reduced MMN amplitudes (with the exception of vowel deviants) and prolonged latencies accompanied by a diminished left-hemisphere advantage across all speech feature types in ASD, with the most pronounced effects in complex, multi-feature conditions. **Significance:** By testing alternative hypotheses and predictions, this exploratory study will clarify the extent to which speech processing differences in ASD reflect cognitive biases (local vs. global, per EPF/WCC/NCH) versus speech-specific neurophysiological disruptions. Findings will advance our understanding of the sensory and integrative mechanisms underlying communication difficulties in ASD, particularly in tonal language contexts, and may inform the development of linguistically tailored interventions.

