#### 1.2.3. The Developmental Imperative: Why Focus on Children?

Studying integration in school-age children (ages 5–10) is essential because this period represents a sensitive window for auditory and language development [54,55]. While foundational auditory plasticity, especially at the level of sensory encoding and language-specific speech representations emerges in infancy and is most pronounced during the first few years of life, higher-order auditory and language-relevant circuits retain plasticity well into childhood, extending through adolescence and adulthood [56,57]. This malleability allows us to capture core processing differences before compensatory strategies or environmental adaptations obscure them.

Moreover, mismatch negativity (MMN) paradigms that do not require focused attention to complete the task are particularly effective in this age group, showing high sensitivity to subtle group differences in auditory processing [20,34]. By focusing on this developmental stage, we can identify early neural markers of integration difficulties—markers that may predict later language outcomes and inform timely, targeted interventions. If integration deficits are rooted in developmental disruptions of neural synchrony or time-binding mechanisms [58,59], then childhood is the optimal window for detecting differences and implementing intervention. Understanding how EPF, WCC, and NCH manifest during this period will not only clarify the cognitive architecture of speech processing in ASD, but also guide the development of culturally and linguistically appropriate strategies to support speech perception and communication.

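### Age is left to exploratory analysis on grounds of power, although adjusting costs almost none; matching rests on a non-significant t-test, and the recruited ages (9–14) do not fit the rationale (5–10)

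*Protocol article*

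**What the plan says.** Section 2.1.2 plans 30 children per group from two schools, each group described as "28 males, 2 females; age range: 9–14". The groups are called matched on gender ratio, non-verbal intelligence and "age (no significant difference between groups as determined by independent samples t-test". No tolerance on the age gap and no pairwise matching is given.

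Section 6 says that symptom severity (GARS-2), age and gender are to be collected but that "these variables could not be fully included as covariates in formal models due to power constraints". It adds: "They can be considered in exploratory analyses".

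Section 1.2.3 gives the developmental rationale: "Studying integration in school-age children (ages 5–10) is essential because this period represents a sensitive window". It links the promise of early neural markers to that stage. Section 5 says: "Our carefully matched ASD and TD sample allows us to examine how factors like language ability, symptom severity, and developmental stage modulate neural processing".

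**The concern.** A non-significant test is weak evidence of balance, because with 30 per group it cannot detect moderate age gaps. If a gap remains and age is related to the ERP measure, part of an apparent ASD–TD difference is an age difference. The usual protection is to put age in the model. Section 6 withholds it from the formal models to save power, but a covariate that predicts the outcome tends to raise power, and one that does not costs very little.

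The age range is a second, independent problem. The sensitive-window argument is made for one age band and the children are recruited from another, so the study may not be able to support the developmental conclusions it announces. The section 5 statement that developmental stage can be examined as a modulator also sits awkwardly with the section 6 statement on age.

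**Working it through.** **Plan's own figure.** The article gives no calculation behind the power argument against covariates, so there is nothing to reproduce on this point. Its sample size of 52 (section 2.1.1) cannot be rebuilt, because the number of measurements and their correlation are not stated. That is a separate matter and is not used below.

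**Inputs.** From the article: n = 30 per group (Abstract, section 2.1.2), α = 0.05, and f = 0.25 (section 2.1.1), which is d = 2f = 0.5 for a two-group contrast. Assumed, because the article does not give them: the age SD, the realised age gap g (in SD), and the within-group age–ERP correlation r. Ranges are shown for each.

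**1. What the t-test tolerates.** Largest non-significant gap = t(0.975, 58) × √(2/30) = 0.517 SD. For an assumed age SD of 1.25 to 1.73 years this is 0.65 to 0.89 years. With ages uniform over 9–14 (SD 1.44) it is 0.74 years.

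**2. How often a real gap passes.** Using the noncentral F distribution with 1 and 58 df and noncentrality 15g², the probability of non-significance is 79% at g = 0.3 and 52% at g = 0.5.

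**3. Bias if age is omitted.** For a single-condition or averaged group contrast, bias = r × g in outcome SDs. The type I error follows from noncentrality 15(rg)².

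**4. Cost or gain of adjusting.** Variance of the adjusted group difference = (1 − r²) × (2/30 + g²/58), with 57 error df instead of 58. Unadjusted power at d = 0.5 is 47.8%.

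| r (assumed) | Bias, g = 0.5 | Type I error, unadjusted, g = 0.5 | Adjusted power, g = 0 | Adjusted power, g = 0.5 |
|---|---|---|---|---|
| 0 | 0 | 5.0% | 47.8% | 45.4% |
| 0.1 | 0.05 SD | 5.4% | 48.1% | 45.8% |
| 0.2 | 0.10 SD | 6.7% | 49.3% | 46.9% |
| 0.3 | 0.15 SD | 8.8% | 51.4% | 49.0% |
| 0.5 | 0.25 SD | 15.9% | 59.4% | 56.8% |

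The worst loss in the table is 47.8 − 45.4 = 2.4 points. At d = 0.74 it is 80.5 − 78.0 = 2.5 points.

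**5. Break-even.** At g = 0.5 the variance inflation is 1 + 0.25/(58 × 2/30) = 1.065. Precision is gained once (1 − r²) × 1.065 < 1, that is r above about 0.25; allowing for the lost df, about 0.25 to 0.3. With balanced ages the gain begins at about r = 0.1.

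**6. The group × condition interaction.** An age effect that is the same in all conditions drops out of each child's between-condition differences, so it cannot bias this interaction. Bias there needs an age effect that varies by condition, and only age × condition terms adjust for it. The df cost is again slight. With 7 conditions, N = 60 and f(V) = 0.5, moving from 53 to 52 denominator df lowers power from 79.0% to 78.9%.

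**7. Age ranges side by side.** Section 1.2.3 argues from 5–10; section 2.1.2 recruits 9–14 in both groups. They share only ages 9–10.

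**The case against.** The plan does not ignore age. Section 6 says the variables are not fully included, allows exploratory use, and discloses this as a limitation of a study described as exploratory. Section 2.1.2 calls the groups matched and cites the t-test as the check; the 52% pass rate describes unselected sampling from populations that truly differ, and deliberate matching may do better. The realised gap and the age–ERP correlation are not in the article, so the bias may be negligible: at r = 0.1 and a 0.5 SD gap, type I error is only 5.4%. All of this stands. It limits the size of the problem but does not make power a sound reason for leaving age out.

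A reader might infer more than the documents support:

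- *That the unadjusted analysis is never more powerful.* With a gap of 0.517 SD the inflation is 1 + 0.517²/(58 × 2/30) = 1.069. At r = 0.2 the adjusted variance is then 0.96 × 1.069 = 1.03 times the unadjusted one, a small loss.
- *That every ASD–TD contrast is biased.* The central hypotheses concern patterns across conditions, and a common age effect cancels in the group × condition interaction.
- *That age must predict the ERP over 9–14.* The article reports no such correlation.
- *That Raven score should also be a covariate, or that the RSA comparison should be age-adjusted.* Section 6 does not list Raven among the omitted variables, and section 2.1.2 says it is matched. Section 2.3.4 does not say whether RSA fits are made per child or per group, so no usable adjustment can be specified.

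**Conclusion.** The point holds for age. A non-significant t-test with 30 per group leaves room for an observed gap of up to 0.52 SD, and the power argument against adjusting is wrong: the cost is 1 of 58 error df and at most about 2.5 points of power, in the case where age is unrelated to the ERP and the gap is 0.5 SD. The possible bias is 0.05 to 0.25 SD in per-condition or averaged contrasts of amplitude and latency, against a planned effect of d = 0.5. This rests on an assumed 0.5 SD gap and r of 0.1 to 0.5, and it may be near zero.

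The argument does not extend to the other two variables. GARS-2 is described only for the ASD group and cannot serve as a covariate in the group contrast, and gender is balanced at 28:2 by design. Nor would age adjustment deal with other confounding, such as language ability.

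The conflict between 5–10 and 9–14 is a plain inconsistency and depends on none of these assumptions. The article does not show which range is intended.

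**What to change.** In section 6, replace the power argument as it applies to age. State that centred, continuous age is a covariate in the ASD–TD comparisons of component amplitude and latency, with age × condition terms wherever the group × condition interaction is tested. Keep GARS-2 for exploratory analysis within the ASD group.

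In section 2.1.2, report the standardized age difference between groups as the evidence of matching, in place of a p-value.

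Reconcile sections 1.2.3 and 2.1.2 on the age range, and limit the developmental-window and early-marker claims to the ages actually recruited.

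The cost is text and model specification only, since age is already to be collected. The statistical price is 1 error df, a few more with age × condition terms, and a small power loss if age turns out to be unrelated to the ERP. The adjustment removes only bias from age imbalance, and only if the age term is suitable (for example, linear with a common slope in both groups).
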